**Figure 1 figure1:**
[figure not shown]
Participant process flow diagram.

The research team will consist of 3 members; the layout of the study room is shown in Figure 2. Research member 1 will indicate to the participant when a new metronome rate starts. After the 20-second warm-up period, research member 1 will indicate the beginning of the 2-minute monitoring period by announcing the word Start. The HCP will start their manual counting of the participant’s RR 30 seconds after the beginning of each new metronome rate; they will be informed by research member 1 when to start counting. They will be given 60 seconds to calculate the manual RR and will be informed by research member 1 when to stop counting. They will then record the RR in the case report form. The participant will continue to breathe at the specified rate for a further 30 seconds (for a total of 2 minutes) and will be informed by research member 1 when the metronome rate has finished so that they return to normal breathing.

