### Study Design

The study is a single-center, prospective observational study to investigate the agreement of the RespiraSense device compared with (1) other device measurements (capnography, ECG) and (2) the current standard measurement of RR (manual counting by a trained HCP). The different methods will be employed concurrently on the same participant as part of a single study visit.

Once participants have provided consent, the following baseline data will be collected:

Demographics (age, sex)Height, weight (to calculate body mass index)Skin assessment at RespiraSense device attachment site (color, texture, uniformity of appearance, integrity). It will also be confirmed that the skin has no discoloration or rash, epidermal loss, blistering, edema, tears, maceration or folliculitisOxygen saturation and pulse oximetry

Participants will be asked to wear a hospital gown and be positioned on an examination couch in the simulation suite. The RespiraSense device, a nasal cannula, and an ECG will be attached and a video recorder positioned to ensure the viewers of the video experience the same image as the HCP performing manual RR monitoring.

A computer-based metronome will be used to produce a repetitive tone at a set rate, which is played to each participant via headphones. The metronome has been produced for the study by the study sponsor team using Microsoft Visual Basic. The metronome rates will be generated using a random number generator program, and the order of the different rates will vary with each participant to ensure the rates are random. The participants will be asked to begin to inspire when each tone is heard and will be given a 20-second warm-up period during which time they will regulate their breathing pattern to match the rate of the tone they hear. Each participant will be asked to breathe at one value from each of the following categories for 2 minutes:

≤8 breaths per minute9 to 11 breaths per minute12 to 20 breaths per minute21 to 24 breaths per minute25 to 29 breaths per minute30 to 35 breaths per minute

One rate will be randomly generated from within each of the 6 categories. Examples of potential sets are shown in Table 2.

**Table 2 table2:** Examples of possible sets of metronome rates to be used.

Participant	First rate	Second rate	Third rate	Fourth rate	Fifth rate	Sixth rate
Participant A	6	10	23	17	28	32
Participant B	5	14	9	22	31	26
Participant C	11	7	13	21	33	27

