**Figure 2 figure2:**
[figure not shown]
Schematic of room layout.

Research member 3, blinded to the rates being played in each metronome rate, will record RR values for the continuous ECG and capnography monitoring and the X Series monitor (Zoll Medical Corp) at 60 and 120 seconds. Research member 2 will press the Start and Stop button on the RespiraSense device at the beginning and end of each 2-minute metronome rate and will record the start and stop time on the case report form.

Following the 10 metronome rates, the participant will then be asked to read a verse from a book for 2 minutes. During this time, their RR will be monitored in the same way as for the 10 metronome rates. Once the participant has finished reading aloud, the study will finish.

Throughout the study procedure, a video recording will be made using the portable Scotia Medical Observation and Training System (Scotia UK Plc), the audiovisual system installed in the simulation suite, which includes an in situ camera system (hardware and software).

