**Figure 3 figure3:**
[figure not shown]
RespiraSense device and data flow.

The system uses a specifically designed adhesive attachment accessory (sensor), which fixes the device to the patient’s chest and contains piezo films that convert breathing motion into an electrical output. The lobe provides and communicates measurement values and technical information such as battery state wirelessly via Bluetooth to the software application hosted on a commercial off-the-shelf tablet computer. It can also provide basic information on activity status of the patient. The application and removal of the elements of the RespiraSense device, along with the maintenance of the device during operation, will be managed by a trained research nurse. Nasal end-tidal CO_2_ monitoring will be performed using Microstream Smart CapnoLine Plus EtCO_2_ sampling line (Zoll Medical Corp) with a disposable adult/intermediate nasal cannula. Data will be collected and automatically logged onto an SD card in the X Series monitor.

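### The text runs each breathing epoch on two incompatible clocks, so it is unclear whether the RespiraSense recording includes the warm-up that the manual count avoids

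*Protocol article*

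**What the plan says.** All of this is in the protocol article, Methods, Study Design, including the text around Figures 1 and 2.

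- **Onset.** "Research member 1 will indicate to the participant when a new metronome rate starts". Participants "will be given a 20-second warm-up period during which time they will regulate their breathing pattern to match the rate of the tone they hear".
- **Monitoring period.** "After the 20-second warm-up period, research member 1 will indicate the beginning of the 2-minute monitoring period by announcing the word Start".
- **Manual count.** It begins "30 seconds after the beginning of each new metronome rate" and lasts 60 seconds. Then: "The participant will continue to breathe at the specified rate for a further 30 seconds (for a total of 2 minutes").
- **RespiraSense.** Research member 2 "will press the Start and Stop button on the RespiraSense device at the beginning and end of each 2-minute metronome rate".
- **ECG and capnography.** Research member 3 records the ECG rate together with "capnography monitoring and the X Series monitor (Zoll Medical Corp) at 60 and 120 seconds". The event from which those seconds are counted is not named.

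The same section gives each metronome rate a length of two minutes and describes the methods as applied concurrently. Data Transfer and Processing says only that the RespiraSense rates will be matched to the other data.

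**The concern.** The primary analysis is the difference between methods and its limits of agreement. Any difference in what the methods were observing is counted as disagreement between them.

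The warm-up is the part of the epoch in which the participant is, by design, not yet at the target rate. If one method's record includes it and another's does not, the difference acquires a component that depends on the target: too high at slow rates, too low at fast ones. The study was set up to test the device at those extremes, and such a pattern could be mistaken for device error there.

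A smaller issue sits beside it. Even with the warm-up excluded everywhere, the count, the device record and the monitor readings do not cover the same seconds.

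**Working it through.** **1. The article's own total.** 30 + 60 + 30 = 120 s, so its two minutes reproduce. The warm-up plus the monitoring period is 20 + 120 = 140 s. One epoch cannot be both if all times share an origin.

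**2. The two clocks, in seconds since tone onset.**

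| Event | All times from tone onset | All times from *Start* |
|---|---|---|
| Warm-up | 0-20 | 0-20 |
| *Start* | 20 | 20 |
| Manual count | 30-90 | 50-110 |
| ECG/capnography readings | 60, 120 | 80, 140 |
| RespiraSense recording | 0-120 | 20-140 |
| End of rate | 120 | 140 |
| Time left after *Start* | 100 | 120 |
| Warm-up seconds in RespiraSense recording | 20 | 0 |

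The first column breaks the two-minute monitoring period, since only 100 s remain after *Start*. The second breaks the wording that times the count and the device from the metronome rate, which the text begins before the warm-up. It also makes the tone last 140 s.

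**3. Possible size, on the first column only.** Assume the RespiraSense value is a plain average over 0-120 s. Then

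error = (20/120) × f × (entry rate − target),

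with f = 1 for no adaptation during the warm-up and f = 0.5 for linear adaptation across it. The entry rate is an assumption: 15/min, with the article's normal adult range of 12 to 20 as bounds.

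| Target | Entry rate | f = 0.5 | f = 1 |
|---|---|---|---|
| 33 | 15 | -1.50 | -3.00 |
| 33 | 12 | -1.75 | -3.50 |
| 33 | 20 | -1.08 | -2.17 |
| 6 | 15 | +0.75 | +1.50 |
| 6 | 12 | +0.50 | +1.00 |
| 6 | 20 | +1.17 | +2.33 |

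If linear adaptation took only 5 s, the error at 33/min would be (5/120) × 0.5 × (15 − 33) = -0.4.

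**4. Effect on the summaries.** Take the midpoints of the six rate categories as 6.5, 10, 16, 22.5, 27 and 32.5 (the lowest assumes a floor of 5, the slowest example in Table 2). Their mean is 114.5/6 = 19.08. With an entry rate of 15 the average error is (15 − 19.08)/6 = -0.68 at f = 1 and -0.34 at f = 0.5, because opposite signs partly cancel. The SD of the error across the midpoints is 1.53 and 0.76 respectively.

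Added in quadrature to the planning SD of 2.5 for the manual comparison, these widen the half-width of the limits from 1.96 × 2.5 = 4.90 to 1.96 × √(6.25 + 0.58) = 5.12 at f = 0.5, and to 1.96 × √(6.25 + 2.34) = 5.74 at f = 1.

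**5. Scale.** The precisions marked in Tables 3 and 4 reproduce:

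- Mean difference: (1.96 × 1.79/0.25)² = 196.9 and (1.96 × 2.5/0.3)² = 266.8 (tabled 197 and 267).
- Limits: 3 × (1.96 × 1.79/0.4)² = 230.8 and 3 × (1.96 × 2.5/0.6)² = 200.1 (tabled 231 and 201).

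The study therefore aims at 0.25-0.3/min for the mean and 0.4-0.6/min for the limits.

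**6. Windows with no warm-up included.** From any common origin the manual count spans 30-90 s, RespiraSense records 0-120 s, and ECG and capnography share readings at 60 and 120 s. That is three timings. The count covers 60 of the 120 RespiraSense seconds, and the second monitor reading comes 30 s after the count has ended.

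**The case against.** The strongest reply is that a coherent reading exists. If the monitoring period opens at *Start*, the sequence 30 + 60 + 30 s fills it exactly, and the two-minute metronome rate that governs RespiraSense can be the same two minutes. The warm-up is then outside every measurement. Figure 1, the process flow, is not available here and may say so. This stands: the contamination is a possibility created by the wording, not an established feature of the design.

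A reader might infer from the button presses that RespiraSense will be analysed as a 120-second average. The article does not say this. The device records continuously, its start and stop times are logged, and the pairing rule may properly be left to the full protocol or analysis plan. The figures above are therefore conditional, and they also depend on how fast participants adapt. At 33/min about 11 tones fall in 20 s, so adaptation could be quick.

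A reader might also infer that unequal windows alone pull RespiraSense towards the spontaneous rate. They do not. Once pacing is steady, all windows target the same rate, and the mismatch adds sampling noise rather than a directional error.

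What the reply does not remove is the conflict in the running text. These timings are stated, and they disagree; they have not simply been left to another document.

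**Conclusion.** The point holds as a contradiction in stated timings that should be resolved before recruitment. Two origins are in use, 20 s apart, and the device under test is tied to the one that, taken literally, includes the warm-up.

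The size lies between zero and the conditional figures. It is zero if all times run from *Start*. With literal timing, whole-recording averaging and an entry rate of 15/min, it is about -1.5/min at 33/min and +0.75/min at 6/min with half adaptation, twice that with none, and less with quick adaptation. Errors of the larger size would exceed the planned precision at the extreme rates, yet would partly cancel in the overall mean. They would show mainly as a slope on the Bland-Altman plot and as wider limits.

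The three measurement timings are a separate, lesser matter. They add noise that could be avoided, and the article gives no basis for putting a figure on it. The documents do not support a claim that RespiraSense will be biased.

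**What to change.** 1. Set time zero at *Start*, after the warm-up, for every method. Make the Study Design text and Figure 1 agree, including whether the two minutes per rate exclude the warm-up.
2. Take the primary comparison over the same 60 s, 30 to 90 s after *Start*. Use the continuous RespiraSense record, the manual count and the video recount. For the monitor, use the X Series log where it holds the rate. The article says "Data will be collected and automatically logged onto an SD card in the X Series monitor" directly after describing capnography, so confirm that the ECG-derived rate is logged too. If it is not, use a screen reading at the end of the window.
3. Keep the 60-second and 120-second readings as a sensitivity analysis.

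The cost is a wording change and, for the most part, extraction of data the study already plans to collect. Each value will rest on fewer breaths at the slowest rates: about 6 rather than 12 at 6/min. Stating the origin explicitly also confirms 140 s of tone per rate, which the team should check against the two minutes described elsewhere. Agreeing the clock beforehand matters because logged start and stop times can be trimmed reliably only if it is known which event triggered them.

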**Figure 2 figure2:**
[figure not shown]
Schematic of room layout.

Research member 3, blinded to the rates being played in each metronome rate, will record RR values for the continuous ECG and capnography monitoring and the X Series monitor (Zoll Medical Corp) at 60 and 120 seconds. Research member 2 will press the Start and Stop button on the RespiraSense device at the beginning and end of each 2-minute metronome rate and will record the start and stop time on the case report form.

Following the 10 metronome rates, the participant will then be asked to read a verse from a book for 2 minutes. During this time, their RR will be monitored in the same way as for the 10 metronome rates. Once the participant has finished reading aloud, the study will finish.

Throughout the study procedure, a video recording will be made using the portable Scotia Medical Observation and Training System (Scotia UK Plc), the audiovisual system installed in the simulation suite, which includes an in situ camera system (hardware and software).

### Ethical Considerations

The study will not be initiated before the protocol and all study relevant material such as the informed consent forms and PIS have received approval/favorable opinion from the Health Research Authority and PHT Research and Development department. Any changes to protocol or relevant study documents will be approved by the sponsor. As RespiraSense is a CE-marked product being used within its intended purpose, regulatory approval is not necessary for this investigation.

### Study Device

The RespiraSense device is based on piezoelectric technology. This technology is in the form of films that are an ultraflat laminated layer of piezo material. This material, when bent or strained, produces a small varying voltage difference. This monitor measures the motion of the chest and abdomen during respiratory effort to measure the RR directly from this motion. The stages of development of these devices are described as fully compliant devices to European Medical Device Standards. RespiraSense is intended to act as a short-term monitoring device to assess RR over time by continuously recording, storing, and periodically transmitting RR data. It has no diagnostic function in this study.

Traceability of each device’s construction will be recorded in the company’s Design History File. Each lobe used on a patient will be recorded in an accountability log with the patient study number. Sensors will not be retained once used and will be disposed of by the patient or the HCP.

During this investigation, the sensor will be attached to the patient’s skin in the chest area using medical grade adhesive that has been tested to and complies with ISO10993 (Biological evaluation of medical devices). The RespiraSense device has the dimensions 100 mm × 55 mm × 15 mm, the sensor weighs 50 grams, and the following risks are listed:

Class IIb medical device which conforms with IEC60601-1:A1:2012 and so no risk of electrical shock as no electrical current is passed through the bodyThe device has low weight and as such is not considered to produce any skin ulcersThe device will be adhered using medical grade tape which will minimize reaction to adhesiveWireless transmission of information conforms to standard Bluetooth communication protocols which are currently used in clinical settingsDiscomfort to the patient is considered minimum as the device in placed in a position where side-lying will not cause added pressure to the patient

The RespiraSense is a noninvasive, body-worn, cableless, battery-powered, respiration rate monitoring device. The system consists of 3 parts as shown in Figure 3: the lobe, sensor, and software application. This figure also shows the final assembled device attached to the patient.

**Figure 3 figure3:**
[figure not shown]
RespiraSense device and data flow.

The system uses a specifically designed adhesive attachment accessory (sensor), which fixes the device to the patient’s chest and contains piezo films that convert breathing motion into an electrical output. The lobe provides and communicates measurement values and technical information such as battery state wirelessly via Bluetooth to the software application hosted on a commercial off-the-shelf tablet computer. It can also provide basic information on activity status of the patient. The application and removal of the elements of the RespiraSense device, along with the maintenance of the device during operation, will be managed by a trained research nurse. Nasal end-tidal CO_2_ monitoring will be performed using Microstream Smart CapnoLine Plus EtCO_2_ sampling line (Zoll Medical Corp) with a disposable adult/intermediate nasal cannula. Data will be collected and automatically logged onto an SD card in the X Series monitor.

### Data Transfer and Processing

Once the participant has completed the study, all data collected by the RespiraSense device will be uploaded to a secure cloud-based storage system from which it will be extracted and analyzed by the team at PMD Solutions Ltd. This data will be anonymized and linked to a specific subject ID number allocated during the study. No participant identifiable data will be transmitted to the team at PMD Solutions Ltd. The RespiraSense-calculated RRs for each participant will then be matched to the data collected by the other methods for analysis.

The study database and video recording files will be stored on secure Trust electronic file servers. The associated file name storing this data will be labeled with the title of the clinical investigation and linked to the subject ID number. This file will be saved for a minimum duration of 5 years and will be made available to national authorities upon request in writing. All digital and paper archives will conform to the requirements of the Data Protection Act (United Kingdom, 2018) which incorporates the standards laid out by the General Data Protection Regulation (European Union, 2016).

### Statistical Analysis

The primary end point is the RR as measured by multiple methods. The primary objective of the analysis is to examine the agreement between the RespiraSense device and the other measurement methods for this end point. The mean difference between each pair of methods will be calculated with 95% confidence intervals. Variances will be tested for nonequality with an *F* test. The distributions of the differences will be examined with Bland-Altman plots. Limits of agreement (LoAs) and proportions of measurements outside the limits will be compared. If the differences between methods markedly increase with their mean, the analysis will be repeated with a log transformation of the measurements. A secondary analysis of agreement by participant position (45 degree sitting vs other positions) for each pair of methods will be performed using an analysis of variance.

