**Objective:**

The primary objective is to assess the accuracy of the RespiraSense device in comparison with other methods currently used in clinical practice. The secondary objective is to assess the accuracy of the RespiraSense device in participants in different positions and when reading aloud.

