### Objectives

This research aims to assess the accuracy of the RespiraSense device in comparison with other methods (capnography, ECG) and standard care (manual RR monitoring) in healthy participants across a range of predetermined RRs. The information from this study will contribute to the evidence base on RespiraSense to enable its use in clinical practice.

This investigation will supplement the following research that has been conducted in demonstrating the efficacy and/or accuracy of RespiraSense in a clinical setting:

“Evaluation of a continuous monitoring device in capturing respiratory rate compared to industry standard and gold standard” (Bangor, study reference PMD-CS-007)“Can respiratory rate predict the risk of deterioration of septic patients?” (Denmark, study reference PMD-CS-006ii)“A quality assurance study of respiratory rate measurements on obese patients with a novel monitoring technology” (Portsmouth, study reference PMD-CS-011)

The primary objective is to assess the agreement of the RespiraSense device with alternative methods of RR counting in healthy participants. Secondary objectives are to (1) explore whether the position of the participant has any effect on the agreement between the RespiraSense device readings and alternative methods of RR counting, (2) explore whether the agreement of the RespiraSense device and alternative RR methods alters when a participant is reading aloud, and (3) establish agreement between manual counting of the RR and retrospective adjudication of video. The exploratory objective is to record any dermatological effects of the device.

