## Discussion

### Rationale for Study Design

The Evaluation of Agreement of Breathing Rates Measured by a Novel Device, Manual Counting, and Other Techniques Used in Clinical Practice (VENTILATE) study will test the accuracy of the RespiraSense device at the extremes of RR. The selection of randomized RRs from within defined categories allows these abnormal RRs to be compared with normal RRs without introducing variability in the participant or the HCP. Additionally, video recording of the study procedures allows for independent sampling and monitoring of the ability of the HCP to manually count the RR by another HCP.

We chose to use healthy volunteers without underlying cardiopulmonary disease. It was not deemed safe or appropriate to use patients exhibiting extremes of RR in an observational study of this type. It was decided that the safest way to observe the RRs of interest for the study would be for healthy volunteers to consciously breathe at a given rate.

There are multiple points of contact during the screening visit to minimize the chance that participants fail to complete the study procedures. In addition to the standard practice of providing a PIS and allowing the participant time to consider what will be required of them during the study, the participants will also experience one of the higher RRs that they will be asked to perform during the study day. We chose to do this with the aim of reducing the number of participants who are unable to complete all of the study procedures.

Although the risk of harm to study participants is low, further measures will be taken to mitigate these risks. The potential risk of feeling unwell after breathing at high or low RRs will be mitigated by allowing participants to rest for longer than scheduled or to stop the procedure entirely should they feel unable to continue. A clinician will be present throughout the study procedures and will be able to stop the study at their discretion if they feel it is not safe or would be inappropriate to continue.

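### Accuracy at extreme respiratory rates is claimed, but the stated analysis is pairwise agreement with no reference method and no use of the set rate or rate categories

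*Protocol article*

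**What the plan says.** The article words its aim in two ways. The Abstract (Objective) says: "The primary objective is to assess the accuracy of the RespiraSense device in comparison with other methods currently used in clinical practice". Rationale for Study Design says that the study "will test the accuracy of the RespiraSense device at the extremes of RR". The Objectives section also opens with an accuracy aim over a range of predetermined rates, but then says: "The primary objective is to assess the agreement of the RespiraSense device with alternative methods of RR counting in healthy participants".

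The Statistical Analysis section follows the agreement wording: "The primary objective of the analysis is to examine the agreement between the RespiraSense device and the other measurement methods for this end point". The contrast is stated plainly: "The mean difference between each pair of methods will be calculated with 95% confidence intervals". An F test of variances, Bland-Altman plots, LoA, and an analysis of variance by position complete the plan. Rate enters only through the horizontal axis of the plots and a log transformation if differences grow markedly with the mean. No method is named as reference.

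Rate is nevertheless the main design variable. Study Design says: "A computer-based metronome will be used to produce a repetitive tone at a set rate, which is played to each participant via headphones". Participants receive one randomly generated rate from each of six categories, then four more rates in another position. Neither the set rate nor the category appears in the analysis.

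**The concern.** A claim about accuracy at extreme rates needs two things: results shown separately at those rates, and something to be accurate against. The stated analysis provides neither.

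Each pairwise LoA carries the error of both methods, so a wide RespiraSense–manual interval does not by itself say which method is at fault. A bias that all methods share at very slow or very fast breathing cancels out of every pairwise difference.

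The study is justified by the scarcity of abnormal values in the earlier 48-patient investigation. A single summary over all rates could leave that gap only partly filled, although the data to fill it are collected.

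**Working it through.** **Inputs.** From Patient Population Size: SD of differences 1.79 (RespiraSense v ECG, also used for capnography) and 2.5 (RespiraSense v manual count); 30 participants with 10 points each. The error SDs of single methods are not given, so they are varied below as assumptions.

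**1. The plan's own figures.** For the mean, N = (1.96 × SD / precision)², rounded up. For the LoA, N = 3 × (1.96 × SD / precision)², rounded up.
- SD 1.79, mean ±0.25: (1.96 × 1.79 / 0.25)² = 196.9, so 197.
- SD 1.79, LoA ±0.4: 3 × (1.96 × 1.79 / 0.4)² = 230.8, so 231.
- SD 2.5, mean ±0.3: 266.8, so 267. LoA ±0.6: 200.1, so 201.

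Every row of Tables 3 and 4 reproduces this way. The tables are not in dispute here.

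**2. Manual error within the RespiraSense–manual difference.** With independent errors, Var(difference) = Var(RespiraSense) + Var(comparator).
- RespiraSense v manual: 2.5² = 6.25. RespiraSense v ECG: 1.79² = 3.20.
- Subtracting: Var(manual) − Var(ECG) = 3.05. Since Var(ECG) cannot be negative, Var(manual) is at least 3.05 (SD 1.75).
- Share of the RespiraSense–manual variance: 3.05 / 6.25 = 49%, as a minimum.
- LoA half-width: 1.96 × 2.5 = 4.90. RespiraSense's own half-width is at most 1.96 × 1.79 = 3.51.

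**3. What the ECG pair leaves open.** RespiraSense's own SD is √(3.20 − ECG error variance):

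| Assumed ECG error SD | RespiraSense own SD | Own half-width | Manual share of 6.25 |
|---|---|---|---|
| 0 | 1.79 | 3.51 | 49% |
| 0.5 | 1.72 | 3.37 | 53% |
| 1.0 | 1.48 | 2.91 | 65% |
| 1.5 | 0.98 | 1.91 | 85% |

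**4. What all pairs together can do.** Under independence, Var(RespiraSense) = [V(RespiraSense, ECG) + V(RespiraSense, manual) − V(ECG, manual)] / 2. In simulation with a true variance of 1.0 this returned 0.998. The planned output would therefore contain the ingredients, but the step is not stated. It recovers error variances, not absolute bias.

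**5. Shared bias and tracking error.** Let the participant breathe at the set rate plus a tracking error t, and let every method share a bias b at that rate.
- Method A minus method B: t and b both cancel.
- Method A minus set rate: t + b + A's own error. The shared bias becomes visible, but so does the tracking error.

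For an assumed own SD of 1.0 and tracking SD of 0 / 0.5 / 1 / 1.5 / 2, the half-width 1.96 × √(1.0² + tracking²) is 1.96 / 2.19 / 2.77 / 3.53 / 4.38. At a tracking SD of 1.5 it is no narrower than the ECG-based ±3.51.

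**6. Precision by category.** The 45-degree position gives one epoch per category per participant, so 30 points before any loss. If the planning SDs hold within a category, the mean difference is known to ±1.96 × 1.79 / √30 = ±0.64, or ±0.89 with SD 2.5. The LoA are known to √3 times that: ±1.11 and ±1.55.

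**The case against.** The strongest reply is that the primary objective in the Objectives and Statistical Analysis sections is agreement, and that the Abstract qualifies accuracy as relative to other methods. Pairwise LoA are the standard summary for agreement. That stands: the planned analysis is not wrong for its stated primary objective.

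Three stronger readings are tempting, and the article does not support them.
- A reader might infer that comparator error is charged to RespiraSense. Nothing in the article attributes the differences to the device. All pairs of methods are compared, and manual counts are also to be checked against adjudicated video.
- A reader might infer that the pairwise results can never separate the methods' errors. That holds for one pair alone, but three pairs together can do so under independence.
- A reader might treat the metronome rate as the true rate. The text says only: "The participants will be asked to begin to inspire when each tone is heard". It is a target. The methods run concurrently on the same breaths, so tracking error cancels in pairwise differences but not against the set rate.

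The other side can also say that capnography is described as accurate in intensive care and ranked above ECG, and that the criticism of manual counting concerns routine practice, whereas here a trained professional counts for a timed 60 seconds. Both are fair. But capnography is given no reference role in the analysis, and a better manual count would lower the 49% without removing the mixing of errors.

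Finally, this is a condensed article and an analysis plan may add a breakdown by rate. The mismatch between the accuracy claims and the stated contrast is nevertheless within the article itself.

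**Conclusion.** The concern holds as a gap between claim and analysis, not as a faulty agreement analysis. The article claims accuracy across set rates and at the extremes, while its stated analysis is pairwise agreement without a reference, a set rate or a rate category.

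On the planning SDs, at least about 49% of the RespiraSense–manual difference variance is manual error, and the ±4.90 LoA compares with at most ±3.51 for RespiraSense's own error. This rests on independent errors, on the same RespiraSense error in both comparisons, and on SDs from an earlier study with few abnormal values carrying over. The share due to ECG or capnography cannot be fixed from the article.

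It would go too far to say that the study cannot address accuracy: the data allow it, and what is missing is a stated step. The change is a worthwhile improvement at little cost.

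**What to change.** - Keep the pairwise mean differences and LoA as the primary agreement analysis. Report them for each pair by set-rate category as well, with a participant random effect wherever a participant contributes more than one epoch.
- As a supporting analysis for the 10 metronome epochs (not reading aloud), report bias and LoA of each method minus the set rate, by category. Repeat it without epochs where the logged capnography shows that the participant left the tone. Capnography is then the arbiter, so its own result in that repeat should not be read as evidence of its accuracy.
- Either name a reference for accuracy claims, for example capnography or the adjudicated video count, or restrict the wording in the Abstract, Objectives and Rationale for Study Design to agreement.

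The cost is a few lines of analysis. The rates are generated by the study's own program, and recruitment had not started. There are two downsides. Estimates by category are less precise (about ±0.6 to ±0.9 for a mean difference and ±1.1 to ±1.5 for a limit, from 30 points), so they should be presented as estimates with intervals. Tracking error enters the set-rate comparison, so an offset seen there in all methods may be shared bias or participants drifting from the tone.
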